## Abstract

**Background:**

Denture-related erythematous stomatitis (DES) is a chronic biofilm-mediated disease, affecting one in every three complete denture wearers. Antifungals are the treatment most commonly prescribed by oral health professionals, based on the belief that colonization by *Candida* spp. is the main cause of DES. However, high recurrence rates and adverse effects are commonly observed, prompting the need for practice guidelines regarding treatment. Results from our pilot study demonstrate that palatal brushing can reduce the palatal inflammation and potentially associated *Candida* carriage without any need for antifungal therapy. The objective of this study is to validate these pilot results by means of a randomized controlled trial (RCT) and provide a practice guideline for clinicians.

**Methods/design:**

A pragmatic, two-parallel-arm, multicenter RCT will be conducted in Canada, Brazil, and Chile. Fifty-two adult complete denture wearers presenting with moderate to severe DES will be allocated randomly to two groups: the Intervention arm will consist of palatal brushing and standard oral and denture hygiene measures, while the Control arm will include only standard oral and denture hygiene measures. The study outcome will be the oral *Candida* carriage. Participants will be assessed at baseline, and at 3 and 6 months post intervention. Descriptive, bivariate, and mixed models with repeated measures will be performed following the intention-to-treat principle.

**Discussion:**

This pragmatic RCT will serve to provide a clinical practice guideline regarding the use of preventive measures in the treatment of biofilm-mediated oral diseases. Moreover, it will have a great impact on reducing the harm of antifungal overtreatment on patients suffering from DES.

**Trial registration:**

ClinicalTrials.gov, NCT02686632. Registered on 15 February 2016.

**Electronic supplementary material:**

The online version of this article (doi:10.1186/s13063-017-1947-y) contains supplementary material, which is available to authorized users.

## Background

Denture biofilm is a complex layer of microorganisms, including bacteria and yeasts, embedded in an extracellular polysaccharide matrix [1, 2]. Toxins and metabolic waste produced by these microorganisms cause cell injury and inflammation [3, 4]. Evidence suggests that microorganisms commonly found in oral biofilms can play a role in the development of systemic conditions through various pathways of infection and inflammation [5–8]. Thus, maintaining the oral microbial ecological equilibrium is critical because it plays a significant role in the prevention of oral diseases and their associated systemic complications [9]. However, many oral biofilm-mediated diseases continue to be treated based on outdated practice guidelines established with weak supporting evidence.

Practice guideline development is a complex process that is impeded by a lack of sound research and scientific evidence. This makes clinical decision-making a challenging task, potentially resulting in adverse consequences for patients, including misdiagnosis, maltreatment, overprescription of medications, unwanted side effects and harm, as well as depletion of resources of the health care system [10–13]. In turn, these consequences may even lead to legal issues for healthcare providers.

Denture-related erythematous stomatitis (DES) is an example of a biofilm-mediated disease treated according to suboptimal practice guidelines. DES is a longstanding and recurrent inflammatory condition, mostly observed on the palatal mucosa and easily diagnosed during routine oral examination. Similar to other types of inflammation, it results from the host’s protective cell response to traumatic, chemical, or microbial cell injury, ensuing vasodilatation, increased microvascular permeability, and tissue edema [14, 15]. While often asymptomatic, some patients may present with mucosal tenderness and bleeding, halitosis, burning sensation, xerostomia, and dysphagia [16, 17]. DES is the most prevalent oral disease and the main indicator of poor oral health among the completely edentate population, affecting one in every three individuals wearing removable dental prostheses [18–22]. A higher prevalence of DES is seen in older people, due to long-term denture use, lack of dexterity in performing oral hygiene, polymedication, and decreased host immunity [23, 24]. However, children and adults wearing acrylic partial dentures, obturator prostheses, and ortho-appliances can also be affected by DES [25–27].

Because complete tooth loss can nowadays be considered a disease of poverty, DES is mostly seen in individuals with low socioeconomic status, who are less likely to visit health care professionals on a regular basis [22, 25, 28]. This may put this population at risk because studies have shown a link between this oral pathology and serious systemic diseases such as bacterial endocarditis and aspiration pneumonia. This is critical for hospitalized patients, individuals with a compromised immune system, and older people with cognitive impairments and dementia [5, 7, 29, 30].

Although the etiology of DES is still undiscovered, the literature at large suggests that this disease is multifactorial, with colonization by *Candida albicans* being the main risk factor [31]. Therefore, clinicians usually prescribe antifungals along with oral hygiene instructions and prosthesis adjustments [32–34]. However, a high recurrence rate and recolonization by *Candida* after cessation of antifungal therapy are widely reported [35–37]. Retreatment with antifungals is therefore common. This unjustified use of antifungal medication may expose patients to adverse effects over time, most notably medication resistance [38]. A recent meta-analysis on this topic showed the inefficacy of antifungals in the treatment of denture stomatitis [39]. Furthermore, several research findings question the etiological role of *Candida* spp. in the initiation of inflammation and suggest that candidal colonization may be secondary to tissue injury and inflammation [40, 41].

Current evidence highlights the need for providing new treatment guidelines for DES. Recent findings from the [name] et al. research group showed that brushing the palate is a promising alternative to antifungal medication [41]. However, these encouraging pilot results should be validated by a randomized controlled trial. A recent systematic review of different treatment methods for DES also highlighted the need for a randomized trial on soft tissue hygiene [42]. Therefore, the objective of this pragmatic clinical trial is to provide evidence on the effectiveness of palatal brushing for the treatment of DES. The knowledge gained from this study will help in developing clinical guidelines aimed at promoting the oral health of edentate individuals.

### Study hypothesis

Edentate individuals with DES using palatal brushing and standard oral hygiene measures after each meal over a period of 6 months will show a clinically meaningful lower level of oral *Candida* carriage when compared with those who use only standard oral hygiene measures.

## Methods/design

### Design

The trial will be a single-blind, parallel group, multicenter randomized controlled trial (Fig. 1). Figure 2 shows the study timeline, according to the Standard Protocol Items: Recommendations for Interventional Trials (SPIRIT) diagram. Additional file 1 presents the SPIRIT checklist.

**Fig. 1 Fig1:**
[figure not shown]
CONSORT study flowchart. Numbers of withdrawn and lost participants will be reported for each follow-up

**Fig. 2 Fig2:**
[figure not shown]
Study schedule: enrolment, allocation, interventions, baseline, and post-intervention assessments

### Setting and location

The study will be conducted at the following four locations:Coordinating centers: Faculty of Dentistry, Université de Montréal and Faculty of Dentistry, McGill University, Montreal, Canada.School of Dentistry of Ribeirão Preto, University of São Paulo, Ribeirão Preto, Brazil.School of Dentistry, Universidad de La Frontera, Temuco, Chile.

Activities in all centers will involve at least two team members who will work directly with participants: a research trainee and a faculty researcher. These members will hold a DDS or equivalent title.

#### Exclusion criteria

Exclusion criteria will be: (1) having oral mucosal lesions apart from DES; (2) having systemic conditions which predispose to *Candida* spp. infection, such as uncontrolled diabetes; (3) having a history of chemotherapy/radiotherapy; (4) having taken or used antibiotics, steroidal agents, or antifungal agents in the 4 weeks prior to the study; (5) being scheduled to replace existing dentures with new ones during the period of the trial; and (6) already using palatal brushing as a routine oral hygiene procedure.

### Planned trial interventions

#### Intervention

Palatal brushing and standard oral/denture hygiene measures.

#### Comparison

Standard oral/denture hygiene measures.

Palatal brushing will be performed as follows: (a) removal of dentures from the oral cavity; and (b) gently brushing the palate using a soft-bristle toothbrush (Oral-B CrossAction Pro-Health; Procter & Gamble, Iowa, IA, USA) for approximately 1 minute without any toothpaste.

Standard oral/denture hygiene measures will be performed as follows: participants will be requested to clean their dentures by: (a) washing the dentures thoroughly in tap water and making sure that there is no visible debris on the internal and external surfaces; (b) placing 2 cm of toothpaste on a denture brush (Oral-B Denture Brush; Procter & Gamble) and brushing internal and external surfaces for approximately 2 minutes; and (c) rinsing thoroughly with tap water.

Participants in both study arms will be required to perform the prescribed procedures after each meal while continuing with their routine denture-wearing habits for the duration of the trial.

### Participant recruitment

Study participants will be recruited through local newspapers and information brochures distributed in dental clinics, dental schools, and residential homes for older people. Respondents at each center will be asked to contact a dedicated telephone number with a voicemail. The research trainees will return the calls to describe the study and to assess major inclusion criteria. Potentially eligible participants will be invited to visit the responsible research center(s) in their home country. During this visit, they will meet with a study coordinator or responsible research trainee who will explain the trial in further detail and assess the candidate’s eligibility criteria. If the candidate does not meet the eligibility criteria and is not enrolled in the study, the reason for exclusion will be recorded.

Eligible candidates will be invited to participate in the study and given sufficient time to read the informed consent and ask any questions pertaining to their participation. After signing the consent form (Additional file 2), the participants will be formally enrolled in the study and baseline assessment will be conducted.

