### Randomization, blinding, and allocation

After baseline assessment, participants will be allocated randomly to each study arm. Off-site computer-assisted, centralized stratified block randomization will be conducted. Stratification will be conducted according to trial centers. Each participant will receive a sequentially numbered, sealed, opaque, and tamper-proof envelope from the trial coordinator at the respective center, containing the concealed allocated intervention. The trial coordinator will give each participant a demonstration as well as verbal and written instructions for following the protocol in their corresponding study arm.

This person will also serve as the contact person for the participants to discuss any issues regarding the study treatments throughout the duration of the trial. The research trainee and all other investigators involved in the study will be blinded to the intervention.

Because of the nature of the intervention, it is not possible to blind the participants. However, all appointments will be organized in such a way as to minimize communication between participants and to prevent potential study contamination. Additionally, participants will be requested to keep their group allocation confidential and not discuss it with the research team involved in the study analysis. The intervention will start the day after the study participants receive the opaque envelopes allocating them to one of the groups.

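### The plan allows a coordinator to assess eligibility and does not bar the one who dispenses a center's blocked allocations from doing so; if they are the same person, the next arm can be guessed better than chance

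*Protocol article*

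**What the plan says.** All references are to the protocol article.

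- **Who judges eligibility.** Under Participant recruitment, candidates who come to the center are told that "they will meet with a study coordinator or responsible research trainee who will explain the trial in further detail and assess the candidate’s eligibility criteria". Either role may do it.
- **Who dispenses allocations.** Under Randomization, blinding, and allocation, each participant receives a "sequentially numbered, sealed, opaque, and tamper-proof envelope from the trial coordinator at the respective center, containing the concealed allocated intervention".
- **Who sees the arm.** The same section continues: "The trial coordinator will give each participant a demonstration as well as verbal and written instructions for following the protocol in their corresponding study arm". The coordinator is also the participants' contact for questions about the study treatments. This person therefore knows every past allocation at the center.
- **Who is blinded.** "The research trainee and all other investigators involved in the study will be blinded to the intervention". The coordinator is not in that list.
- **How allocation is generated.** "Off-site computer-assisted, centralized stratified block randomization will be conducted", with center as the stratification factor. Allocation follows baseline assessment.

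No sentence separates the eligibility role from the dispensing role.

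**The concern.** Sealed, numbered envelopes hide the content of the next envelope. They do not hide what earlier envelopes contained from the person who handed them out and taught the procedure. In a balanced block within a center, that history carries information about the next assignment. Anyone holding it who also decides who enters can, knowingly or not, let the expected arm influence a borderline decision.

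There is room for judgement. Eligibility depends on grading the stomatitis as moderate to severe, on the absence of other mucosal lesions, and on whether a systemic condition such as diabetes is uncontrolled. The Data collection section also allows a second visit before baseline for candidates who need time to reflect. Deferral is thus a legitimate step that changes which numbered envelope a person receives. A motive is conceivable: brushing after each meal demands adherence, and the section on risks reports mild pain and minor bleeding in 40% of the 48 pilot participants.

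What is at stake is the comparability of the arms at entry, in a trial of 26 per arm.

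**Working it through.** The plan gives no figure for predictability, so there is none to reproduce. The check asks how well an observer who knows all earlier allocations at a center can guess the next one.

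**Inputs**
- Total 52, 26 per arm (Sample size).
- Four locations, two of them in Montreal (Setting and location). Average center size is 52/4 = 13, or 52/3 ≈ 17 if Montreal is a single stratum (assumption).
- Block size is not stated. Sizes 2, 4, 6 and 8 are assumed as a range.

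**Block size known.** Write the block size as b = 2m. The observer guesses the arm with more places left in the block, and tosses a coin when they are equal.

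For b = 4, position by position:
- Position 1: 1/2.
- Position 2: 2/3.
- Position 3: the first two are alike with probability 1/3 (guess certain), otherwise balanced, so 1/3 + (2/3)(1/2) = 2/3.
- Position 4: 1.
- Sum 2.833 of 4, or 70.8% correct. Certain assignments: 1/3 + 1 = 4/3 per block, or 33.3%.

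In general the certain share is 1/(m + 1). Enumerating all balanced blocks gives:

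| Block size | Assignments certain | Guesses correct |
|---|---|---|
| 2 | 50% | 75.0% |
| 4 | 33.3% | 70.8% |
| 6 | 25% | 68.3% |
| 8 | 20% | 66.6% |

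**Certain assignments among 52, blocks of 4.** If all 52 fell in complete blocks: 13 × 4/3 = 17.3. With four centers of 13, each completes 3 blocks, so 12 × 4/3 = 16. With centers of 17, 17 and 18, each completes 4 blocks, again 12 × 4/3 = 16; the one or two left over at each are never certain. Hence about 16–17.

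**Block size unknown.** The observer guesses whichever arm is behind at the center so far (simulation, 30,000 runs per setting):

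| Blocks | 13 per center | 17 per center |
|---|---|---|
| 2 | 73.1% | 73.5% |
| 4 | 69.2% | 69.6% |
| 6 | 66.9% | 66.5% |
| 8 | 63.3% | 65.6% |
| random 2/4 | 70.4% | 70.8% |
| random 4/6 | 67.2% | 67.8% |
| random 2/4/6 | 68.4% | 68.8% |
| random 4/6/8 | 66.0% | 66.5% |

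**Assessor unaware of past allocations.** 50%.

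These figures measure predictability. They do not estimate bias in the treatment effect, which would also depend on how often an assessor acted on a guess and how strongly the selected trait relates to *Candida* counts. The document gives neither.

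**The case against.** The strongest reply is that the overlap is not established. One section says study coordinator and the other trial coordinator, and the text never equates them. The research trainee is a named alternative assessor, and the trainee also makes the telephone screen. Setting and location describes the staff working directly with participants as at least a research trainee and a faculty researcher, and mentions no coordinator there. This stands: the overlap is permitted, not shown.

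Second, concealment is otherwise well described: off-site generation, tamper-proof envelopes, allocation only after consent and baseline. This stands too, but none of it prevents inference from past allocations.

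A reader might go further in four ways that the documents do not support:

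- *That nothing in the plan would reveal selection.* Reasons for exclusion are recorded, extensive baseline data are collected before allocation, examiners are calibrated, and palatal photographs serve a diagnostic consensus. These are partial safeguards. The plan does not say that the consensus precedes enrolment, and deferral, discouragement or selection on unmeasured traits could escape them.
- *That candidates could be selected directly on Candida load.* Counts need 48 hours of incubation, and eligibility is judged before baseline, so the assessor does not know them. Any route runs through visible severity or expected adherence.
- *That assignments are known in advance.* Certainty requires knowing the block size, and nothing says the centers know it. Without it, guesses are only better than chance.
- *That the block scheme is deficient.* An article may leave block size to the full protocol, so its absence is no finding. Varied blocks may already be in use, and the simulation still gives 66–71% correct guesses with them.

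**Conclusion.** The point holds in conditional form. The plan expressly allows a coordinator to assess eligibility, gives each center's coordinator full knowledge of past allocations, and nowhere keeps the two tasks apart. If one person does both, the next arm can be guessed correctly about 67–75% of the time with a known block size of 2 to 8, or about 63–74% with an unknown one, instead of 50%. The range rests on assumed block sizes, on average center sizes of 13 or about 17 for the unknown-size figures, and on an observer who keeps track of the history.

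This is an avoidable opening for selection bias in an otherwise concealed randomization. It is not evidence that selection has occurred, and its effect on the result cannot be quantified from the document. Because the remedy uses roles already in the plan, it is worth closing.

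**What to change.** In Participant recruitment, remove the words *study coordinator or*, so that only the blinded research trainee or a blinded faculty researcher explains the trial, assesses eligibility and signs it off. In Randomization, blinding, and allocation, add that whoever dispenses allocations takes no part in eligibility decisions and first meets the participant after that sign-off and the baseline assessment, to hand over the envelope and give the demonstration.

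The article reports that recruitment is under way, so apply this to all remaining entries. An assessor unaware of past allocations is back at 50%, whatever the block size, so no change to the block scheme is requested.

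The cost is a change of wording, a reallocation of tasks among staff already on site, and slightly less flexibility in scheduling screening visits.

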### Randomization, blinding, and allocation

After baseline assessment, participants will be allocated randomly to each study arm. Off-site computer-assisted, centralized stratified block randomization will be conducted. Stratification will be conducted according to trial centers. Each participant will receive a sequentially numbered, sealed, opaque, and tamper-proof envelope from the trial coordinator at the respective center, containing the concealed allocated intervention. The trial coordinator will give each participant a demonstration as well as verbal and written instructions for following the protocol in their corresponding study arm.

This person will also serve as the contact person for the participants to discuss any issues regarding the study treatments throughout the duration of the trial. The research trainee and all other investigators involved in the study will be blinded to the intervention.

Because of the nature of the intervention, it is not possible to blind the participants. However, all appointments will be organized in such a way as to minimize communication between participants and to prevent potential study contamination. Additionally, participants will be requested to keep their group allocation confidential and not discuss it with the research team involved in the study analysis. The intervention will start the day after the study participants receive the opaque envelopes allocating them to one of the groups.

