### Data collection

Data collection will be conducted using a self-administered questionnaire and a clinical examination conducted by trained and calibrated dentists using a front surface mirror and probe (XP23/QW; Hu-Friedy, Chicago, IL, USA). Photographs of the palate will be taken with a Nikon D90 camera (105 mm f/2.8 D, macro flash SB-21; Nikon Co., Tokyo, Japan). These photographs will be used to obtain a diagnostic consensus from research team members.

To facilitate conducting the study, baseline data will be collected at the participant’s first visit to the research center, following informed consent. However, if the candidates need more time to reflect on their participation and commitment to the study, another visit will be scheduled for baseline assessment. Follow-up data collection will be conducted at 3 and 6 months post randomization by the same examiner at each research center. The data collection sessions are estimated to last approximately 45–60 minutes.

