### Biological sample collection and analysis

Collection of denture biofilm will be performed following the standardized sonication technique protocol [44, 46, 47]. Palatal biofilm will be collected using a sterile swab on the central palatal mucosa (1 cm^2^) [48], placed in a sterile tube with 5 ml saline, and sonicated for 2 minutes. In order to standardize the collection time, samples will be collected between 9 a.m. and 12 p.m. The biological samples will be immediately transferred to the microbiological laboratory at each center.

Swabs and sonicates will be mixed separately with saline, diluted according to the defined protocol [44], inoculated on Sabouraud-Dextrose 4% agar for *Candida* spp., and incubated at 37 °C for 48 hours. Identification of different *Candida* species will be confirmed by growth on selective culture medium (CHROMagar Candida, Paris, France). CFUs will be counted and expressed as CFU/ml, after correction for volume and dilution factor.

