### Statistical analysis

Data entry and analysis will be conducted in a blinded fashion. An interim analysis has not been planned due to the low frequency of adverse effects observed during the pilot trial [41]. Basic descriptive statistical analyses will be performed for all variables after being tested for normality.

Bivariate analysis, as well as mixed-model analyses for repeated measures, with time and intervention as independent variables, will be conducted following testing for normality. In the case of non-normal distribution, the Brunner Langer nonparametric test will be used.

All analysis will be performed in adherence to the intention-to-treat principle [49]. *p* ≤ 0.05 will be considered statistically significant. All analysis will be performed using SPSS version 24 and SAS 9.4 for Windows.

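### Center stratifies the randomization but is not named in the mixed model or its nonparametric replacement, so the test is conservative to the extent that center affects the analysed response.

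*Protocol article*

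**What the plan says.** Under Randomization, blinding, and allocation, the article states: "Off-site computer-assisted, centralized stratified block randomization will be conducted". The next sentence names the only stratification factor: "Stratification will be conducted according to trial centers".

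Two other sections tie measurement to center. Under Biological sample collection and analysis: "The biological samples will be immediately transferred to the microbiological laboratory at each center". Under Data collection, follow-up is done "by the same examiner at each research center". Laboratory and examiner are therefore both aliased with center. Setting and location names four sites in Canada, Brazil and Chile, two of them coordinating centers in Montreal.

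Under Statistical analysis, the main method is "mixed-model analyses for repeated measures, with time and intervention as independent variables". The alternative is: "In the case of non-normal distribution, the Brunner Langer nonparametric test will be used". Center appears in neither, and it is not among the variables listed under Explanatory variables.

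**The concern.** Blocked randomization within center keeps the arms nearly balanced in each center, so between-center differences largely drop out of the treatment comparison. A model without center still counts that variance as residual. The reported standard error is then larger than the true sampling spread of the estimate, intervals are too wide, and the test rejects less often than 5% under the null. In a trial of 52 participants that is precision given away, and the analysis does not match the design.

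Center could plausibly matter here. CFU counts depend on local sampling, culture and counting, and the Discussion presents the mix of populations across international centers as a strength.

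**Working it through.** **Inputs.** From Sample size: a between-arm difference in mean change of 30,000 CFU/ml, SD of change 31.6, power 85%, dropout 10%, 26 per arm. From Statistical analysis: significance level 0.05.

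Assumptions:
- The SD is read as 31.6 thousand. Taken literally as 31.6 CFU/ml, the formula gives 1 participant per arm.
- The test is two-sided.
- There are three strata with arms balanced inside each (8, 8 and 7 per arm).
- Center explains a share R of the change-score variance. The documents give no value, so R runs from 0 to 0.30.

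**The plan's own figure.** n per arm = 2 × (1.960 + 1.036)² × (31.6/30)² = 2 × 8.976 × 1.1095 = 19.9, so 20. With dropout, 20/0.9 = 22.2, so 23 per arm and 46 in total. The t-based calculation gives 21, then 24 per arm and 48 in total. The stated 52 is not reproduced, but it is not too small for these inputs, and this is a separate matter. Completers: 52 × 0.9 = 46.8, taken as 23 per arm.

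**Approximate formulas.**
- Reported SE without center: 31.6 × √(2/23) = 9.32 thousand.
- True sampling SD under balanced stratification: 9.32 × √(1 − R).
- Overstatement of the SE: 1/√(1 − R), which is 1.05, 1.12 and 1.20 at R = 0.10, 0.20 and 0.30.
- Actual type I error: about 2 × [1 − Φ(1.96/√(1 − R))], which is 3.9%, 2.8% and 1.9%.

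**Simulation.** 20,000 trials per value of R, total SD held at 31.6 thousand, least-squares comparison of change with and without center as a fixed effect:

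| R (assumed) | Mean SE without → with center (thousands) | Type I error without center | Power without → with center |
|---|---|---|---|
| 0 | 9.25 → 9.25 | 5.1% | 88.6% → 88.6% |
| 0.05 | 9.28 → 9.03 | 4.6% | 88.6% → 89.6% |
| 0.10 | 9.30 → 8.80 | 3.8% | 89.3% → 91.2% |
| 0.20 | 9.29 → 8.26 | 2.9% | 90.4% → 94.2% |
| 0.30 | 9.34 → 7.76 | 2.0% | 91.7% → 96.2% |

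With center in the model the type I error is about 5% throughout. At R = 0.20 the reported SE without center is 9.29, against a true sampling SD of 8.42. The power differences are 0, 1.0, 1.9, 3.8 and 4.5 points.

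Power without center rises with R because stratified allocation shrinks the true spread of the estimate even when the model ignores center. The comparator is therefore not a fixed 88%.

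**Which contrast is affected.** A smaller simulation (120 runs per scenario) fitted a random-intercept model to baseline, 3 and 6 months:

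- *Constant additive center shift.* The SE of the treatment-by-time contrast at 6 months is 9.30 without center, 9.30 with center and 9.28 with center-by-time, so there is essentially no effect. The SE of the overall intervention effect, in a model without interaction, is 9.15 without center and 7.41 with it.
- *Change itself differs by center.* The SE of the treatment-by-time contrast is 9.96 without center, still 9.96 with a center main effect only, and 9.29 with center-by-time.

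The loss therefore depends on the contrast, and a center main effect alone does not recover it for a time-specific change contrast.

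**The case against.** The best defense is that naming time and intervention does not say they are the only terms. The article plans a time-dependent hygiene variable that the Statistical analysis section also does not name, so the list may be shorthand for the effects of interest. The random part of the model is unstated, and a full analysis plan may add center. This stands as a limit: a reader might infer that the sponsor has decided to exclude center, and the text does not show that. It does, however, list independent variables and omit the only stratification factor, so an analyst following it would leave center out.

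Second, the outcome is a decrease and the sample size rests on change, from which a constant center shift cancels. That is correct for the treatment-by-time contrast. It does not cover the overall intervention effect, or center differences in change. Laboratory differences in raw CFU/ml could be multiplicative and so carry into change, but that is an assumption.

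Third, calibrated examiners, a standardized sonication technique, a defined dilution protocol and a fixed collection window should reduce center differences. This is fair. It is why R = 0 and R = 0.05 belong in the range, where the loss is 0 to 1 point.

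Stronger readings are tempting. A reader might infer losses of about 3, 6 and 8 points at R = 0.10, 0.20 and 0.30 by setting 91%, 94% and 96% against a constant 88%. That overlooks the gain that stratification gives the unadjusted analysis. A reader might also infer false positives or an underpowered trial. The error is in the conservative direction, and power without center is at least 88.6% in every scenario.

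**Conclusion.** The point holds as a modest, conditional inefficiency. The stated model does not reflect the stratified design. To the extent that center affects the analysed response, the SE is overstated and the test conservative. For R from 0 to 0.30 the type I error goes from about 5% to 2.0% and the power loss from 0 to about 4.5 points.

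This rests on an assumed R, on reading the SD as 31.6 thousand, on 23 completers per arm and on balance within centers. For a treatment-by-time contrast it also requires that change differs by center. The documents do not establish that center is a major source of CFU variance. The case for acting is that at R = 0 adjustment costs essentially nothing (88.6% either way), while at larger R it restores the nominal error rate and recovers power.

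**What to change.** In Statistical analysis, add center, defined as the randomization stratum, as a fixed effect in the mixed model. If a time-specific change contrast is primary, add center-by-time as well. State that the Brunner-Langer analysis, which replaces the mixed model under non-normality and is not a sensitivity analysis, will be stratified by center. Showing the treatment effect by center descriptively would help readers.

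State whether the two Montreal sites form one stratum or two. The center term costs 2 degrees of freedom with three strata (3 − 1) or 3 with four (4 − 1). Center-by-time over three visits adds 4 (2 × 2) or 6 (3 × 2). No new data, visits or participants are needed. If a separate analysis plan already includes center, the article's wording only needs to be aligned with it.
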